## **2. Purpose and Significance of the Study**

### **2.1. Background and Objectives**

Hemiplegia occurring in patients after stroke impairs activities of daily living and quality of life. Recovery of upper limb function is a critical goal of rehabilitation therapy. Effective rehabilitation interventions require accurate assessment tools to evaluate treatment outcomes. The Action Research Arm Test (ARAT) is the gold standard assessment tool for evaluating upper limb function in patients with stroke. The ARAT was developed by Lyle in 1981. It is an assessment method. It has excellent psychometric properties . In Japan, the ARAT has been widely adopted as the standard upper limb function assessment tool in both clinical and research settings.

However, the import of the conventional ARAT was discontinued, creating significant challenges for both clinical practice and research. Consequently, a domestically produced version of the instrument was developed. The new ARAT incorporates some modifications to the instrument specifications. While these changes may appear minor, findings from standardized assessment research indicate that even slight alterations in instrument characteristics can potentially affect task difficulty, movement strategies, and measurement precision . Introducing the modified instrument without rigorous psychometric validation risks undermining the continuity of research data and clinical practice standards established over decades by the conventional ARAT.

The purpose of this study is to establish the psychometric properties of the newly developed ARAT by assessing intra-rater reliability, inter-rater reliability, criterion-related validity against the conventional ARAT, and convergent validity with established clinical measures in patients with hemiplegia following stroke. This validation ensures a smooth transition from the conventional ARAT to the newly developed ARAT, maintaining measurement accuracy and clinical utility.

## **3. Methods**

### **3.1. Research Design**

This was a single-center, cross-sectional study.

### **3.2. Methods**

#### **3.2.1 Research Outline**

In this study, participants will be assigned to a group for examiner reliability and inter-rater reliability (reliability validation group) and a group for criterion-related validity (validation group), and validation will be conducted according to the respective protocols.

- Reliability Verification Group

To verify intra-rater reliability, a single examiner performs two new ARATs at 15-minute intervals. During the initial assessment, the examiner will video record the subject's movements for all 19 tasks. To verify inter-rater reliability, a second examiner scores the video recordings without knowing the results of the first examiner's scoring.

- Validation group

A single examiner will administer both the new ARAT and the traditional version of the ARAT to verify criterion-relevant validity. The order of administration will be randomized using a random number table.

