### 3.2.3. Case Registration and Allocation Methods

Participants who meet eligibility criteria will be randomly assigned to either the reliability or validity validation group using a random number table. Group assignment and randomization of assessment order will be performed using a computer-generated random number sequence by the study coordinator, who will not be involved in data collection.

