#### **4. Sample size and study period**

##### **4.1. Sample size**

Total of 60 participants.

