##### **4.2. Basis for setting**

The sample size for reliability verification was calculated based on prior research, assuming ICC = 0.8, minimum acceptable ICC = 0.6,  $\alpha = 0.05$ , power  $(1 - \beta) = 0.8$ , two raters, and two measurements per participant . This calculation indicated a required sample size of 28–30 participants. For criterion-related validity, G\*Power 3.1 was used with an expected correlation coefficient  $r = 0.75$ ,  $\alpha = 0.05$ , and power = 0.95, yielding a minimum target sample size of 16 participants. Considering potential 10% data loss, 30 participants per group were planned.

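### Only the reliability group is filmed, so the inter-rater ICC rests on 30 of the 60 participants who perform the new ARAT and falls short of the stated 80% power

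*Protocol*

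**What the plan says.** Section 3.2.1 describes two groups with separate procedures. In the reliability group one examiner gives the new ARAT twice, 15 minutes apart, and films the first occasion: "During the initial assessment, the examiner will video record the subject's movements for all 19 tasks". The recordings then go to another rater: "To verify inter-rater reliability, a second examiner scores the video recordings without knowing the results of the first examiner's scoring".

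For the validation group the same section says: "A single examiner will administer both the new ARAT and the traditional version of the ARAT to verify criterion-relevant validity". The order of the two versions is randomised. No filming and no second scorer are mentioned for this group, and no reason is given for leaving them out.

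Section 3.2.3 allocates patients at random: "Participants who meet eligibility criteria will be randomly assigned to either the reliability or validity validation group using a random number table". Section 4.1 gives the size as "Total of 60 participants", and section 4.2 splits it equally: "Considering potential 10% data loss, 30 participants per group were planned". The reliability calculation in section 4.2 assumes an ICC of 0.8 against "minimum acceptable ICC = 0.6", with alpha 0.05, power 0.8, two raters and two measurements per participant, and arrives at 28–30. Section 3.5 names ICC (2,1) for both intra-rater and inter-rater reliability, and a quadratically weighted kappa for the items.

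**The concern.** Two of the study's aims need separate groups. Intra-rater reliability needs a second new ARAT, and criterion validity needs the conventional ARAT. Inter-rater reliability needs neither. It needs one live-scored new ARAT and a recording of it for a second rater, and every participant in both groups supplies the performance. Half of those performances go unrecorded, and an unfilmed performance cannot be recovered at analysis.

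This would matter little if 30 were enough. For an ICC built on two ratings per participant, 30 is too few on the protocol's own planning values. The inter-rater ICC, the item-level kappas between raters and any inter-rater measurement error would all be less precise than they could be with the patients already planned.

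**Working it through.** **Inputs (section 4.2).** Expected ICC 0.8, minimum 0.6, alpha 0.05, power 0.8, 30 per group, 10% loss. Sidedness is not stated, so both are shown (z = 1.645 or 1.960; z = 0.842 for 80% power).

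**Formula.** The usual approximation for testing an ICC against a minimum value, with k ratings per participant:

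N = 1 + 2k(z_α + z_β)² / [(k − 1)(ln C)²], where C = (1 + kθ₀)/(1 + kθ₁) and θ = ICC/(1 − ICC).

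Here θ₀ = 0.6/0.4 = 1.5 and θ₁ = 0.8/0.2 = 4.

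**Reproducing the stated 28–30.**

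| Ratings k | C | N one-sided | N two-sided |
|---|---|---|---|
| 2 | 4/9 | 38.6 → 39 | 48.7 → 49 |
| 3 | 5.5/13 | 26.1 → 27 | 32.8 → 33 |
| 4 | 7/17 | 21.9 → 22 | 27.6 → 28 |

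The lower end, 28, appears only with four ratings and a two-sided test, that is, if two raters times two measurements are treated as four exchangeable ratings. No ICC in the design uses four. The intra-rater ICC compares one examiner's two occasions. The inter-rater ICC compares a live score with a video score of one occasion. Both have k = 2.

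**Power with k = 2.** Here ln(4/9) = −0.811. Rearranging, z_α + z_β = √[(N − 1)(0.811)²/4], and power = Φ(that value − z_α). For N = 30 the value is 2.183, so power is Φ(0.539) = 70% one-sided and Φ(0.224) = 59% two-sided.

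| Participants in the inter-rater ICC | One-sided | Two-sided |
|---|---|---|
| 27 (30 less 10%) | 66% | 54% |
| 30 (as planned) | 70% | 59% |
| 45 (new ARAT taken first) | 85% | 77% |
| 54 (60 less 10%) | 90% | 84% |
| 60 (both groups) | 93% | 88% |

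An exact one-way F test agrees within a percentage point: 70% and 58% at 30, 93% and 87% at 60.

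The 45 is the 30 reliability participants plus half of the 30 validation participants, assuming that the randomised order splits equally. After 10% loss it is about 40, with power 81% and 72%.

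**Precision.** At an observed ICC of 0.80 the F ratio is 1 + 2 × 4 = 9. The one-way 95% interval is 0.62–0.90 at n = 30 and 0.69–0.88 at n = 60. This leaves out the rater variance that ICC (2,1) includes. With two raters, more patients do not reduce that component. In a simulation with a true ICC of 0.80 and rater variance set, as an assumption, at 5% of the total, the central 95% of estimates runs from about 0.59–0.60 to 0.91 at n = 30 and from 0.63 to 0.89 at n = 60. With rater variance of 2% or less, the gain is close to the one-way figures.

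**The case against.** The best defence is that nothing here is contradictory. The protocol states the split openly and sizes each group for its own question, and almost any study improves with more data. On the stated requirement of 28–30, thirty participants suffice and pooling is a surplus. The harm thus depends on that requirement being too low for a two-rating ICC, which is a sample-size fault in section 4.2. This stands as description: the point is an inefficiency fixed in the design, not an inconsistency. It does not remove the point, because 30 does fall short and the further performances take place anyway.

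Three limits on pooling also stand:

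- **Raters.** Random allocation makes the patients comparable but says nothing about the raters. Section 3.2.1 refers to a single examiner separately for each group and never says that it is the same person. With different live examiners, pooling would mix two rater pairs, and a fully crossed ICC (2,1) would not apply directly.
- **Order.** About half of the validation participants would take the new ARAT second. The live examiner would by then have scored the same patient on the conventional version, while the video rater would not. Scoring the same performance does not remove this carry-over, because it affects only one of the two raters.
- **Precision.** The one-way interval is a best case.

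A reader might infer that pooling secures 80% power whatever is assumed, or that it repairs reliability as a whole. Neither follows. In the subset that takes the new ARAT first, two-sided power stays below 80%. Intra-rater reliability needs a repeat test that the validation group does not have.

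**Conclusion.** The point holds as a cheap improvement to the design. As written, the inter-rater ICC has about 70% (one-sided) or 59% (two-sided) power on the protocol's own inputs instead of 80%. Using every new ARAT performance would raise this to at most 93% or 88%, or to 90% or 84% after the planned loss, with nobody else enrolled.

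These figures assume a true ICC of 0.8, two ratings per participant, negligible rater variance and a common rater pair. If the true ICC is well above 0.8, thirty may be enough, but 0.8 is the value the protocol planned on. The narrowing of the interval from 0.62–0.90 to 0.69–0.88 should be read as an upper limit on the gain. The protocol does not support a claim that the groups can be pooled without conditions, since it does not fix who examines whom.

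**What to change.** In section 3.2.1:

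- Film the new ARAT in the validation group as well, all 19 tasks, and have the same second examiner score these recordings blind to the live scores.
- State that the same live examiner serves both groups. If not, estimate agreement by rater pair.

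In section 3.5:

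- Estimate the inter-rater ICC (2,1) and the item-level inter-rater kappas on both groups combined (up to 60).
- Add a sensitivity analysis restricted to participants who took the new ARAT first (about 45).
- Keep intra-rater reliability in the reliability group and criterion validity in the validation group.

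In section 4.2, restate the power for a two-rating ICC. Intra-rater reliability remains at n = 30, so its power is still about 70% or 59%.

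The cost is about 30 more recordings for the second examiner to score, filming by the live examiner in a second group, consent wording that covers filming in both groups, and secure storage of the additional, potentially identifiable videos. It adds no patients and no patient tasks. It can apply only to participants not yet assessed; for anyone already tested without filming, the report should give the inter-rater n and the power actually achieved.

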## 3.5 Statistical analysis

Participant characteristics, clinical assessment data: descriptive statistics

Intra-rater reliability: ICC (2,1)

Inter-rater reliability: ICC (2,1)

Measurement error: standard error of measurement (SEM)

Minimum detectable change: MDC95

Item-level agreement: weighted kappa coefficient with quadratic weighting.

Criterion-related validity: Bland-Altman analysis, Bland-Altman plots.

Convergent validity: Correlation analysis

Analyses were performed using Jamovi version 2.6.44 (<https://www.jamovi.org>). The statistical significance level is 5%.

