## 8.3. Anticipated Risks

All upper limb function assessments conducted in this study are performed within the scope of routine clinical practice, and no new risks arise from this research. Patients may experience physical and mental fatigue or feel unwell due to examinations and evaluations. These are matters also observed during routine clinical care.

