## 8.4. How to minimize risk

The examiner will conduct the assessment while observing whether participants appear excessively tense and inquiring about their physical and mental fatigue levels. During evaluation, appropriate rest periods will be scheduled as needed, taking care to minimize physical and mental strain as much as possible. If continuing the study becomes difficult, it will stop immediately. Should any participant report feeling unwell, this will be reported to the rehabilitation physician for appropriate examination and treatment

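### The order of the two ARAT versions is randomised, but section 3.5 makes no stated use of it; an order term would remove any practice or fatigue effect from the limits of agreement at almost no cost

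*Protocol*

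**What the plan says.** Protocol 3.2.1 has one rater for the validation group: "A single examiner will administer both the new ARAT and the traditional version of the ARAT". On sequence it says "The order of administration will be randomized using a random number table". Section 3.2.3 adds "Group assignment and randomization of assessment order will be performed using a computer-generated random number sequence by the study coordinator", and keeps that coordinator out of data collection. Neither section says whether the order is blocked or split equally.

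Section 3.5 gives the analysis in one line: "Criterion-related validity: Bland-Altman analysis, Bland-Altman plots". It neither includes nor excludes an order term. Section 4.2 plans 30 participants per group, allowing for 10% data loss.

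On possible order effects, section 8.3 says "Patients may experience physical and mental fatigue or feel unwell due to examinations and evaluations", and section 8.4 says "appropriate rest periods will be scheduled as needed". The reliability group has a 15-minute interval between its two administrations; no interval is stated for the validation group.

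**The concern.** The validation group is in effect a two-period crossover of two instruments. If patients do systematically better (practice) or worse (fatigue) on the second test, that effect enters the new-minus-conventional difference with a plus sign when the new version comes second and a minus sign when it comes first. An analysis that pools all differences counts this session effect as disagreement between the instruments.

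The stated purpose is a smooth transition from the conventional to the new ARAT, and no agreement margin is set. Readers will therefore judge interchangeability largely from the bias and the width of the limits. The trial already generates the order, so the information needed to separate the session effect is there to be used.

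**Working it through.** **The plan's own figure.** Section 4.2 derives 16 participants for criterion-related validity from r = 0.75, α = 0.05 and power 0.95. This reproduces: under a bivariate normal model with a two-sided test, simulated power is 0.952 at n = 16 and 0.937 at n = 15. The Fisher z formula gives ((1.960 + 1.645)/atanh(0.75))² + 3 = 16.7, so 17. The figure concerns a correlation and says nothing about the width of the limits, so it neither supports nor weakens the point.

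**Inputs for the point.** n = 30 comes from section 4.2. The second-minus-first effect p and the within-order SD of the differences s are not in the protocol. Both are assumptions, so results are given as a range of p/s.

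**Model.** Let d = new minus conventional. Then d = bias + p + e when the new version is second, and d = bias − p + e when it is first, with SD(e) = s.

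**Width of the limits.** With the orders pooled and equally frequent, Var(d) = s² + p². The limits widen by √(1 + (p/s)²):

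| Assumed p/s | Factor | Widening | Movement of each limit, 1.96 × (factor − 1) |
|---|---|---|---|
| 0.10 | √1.01 = 1.005 | 0.5% | 0.01 s |
| 0.25 | √1.0625 = 1.031 | 3% | 0.06 s |
| 0.50 | √1.25 = 1.118 | 12% | 0.23 s |

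For example, if s were 2 points, the half-width of 1.96 × 2 = 3.92 points would become 4.04 with p = 0.5 point and 4.38 with p = 1 point. Simulation with n = 30 gave the same two values.

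**Observed bias.** With n1 and n2 patients in the two orders, the pooled mean difference moves by p(n1 − n2)/n: 0 at 15:15, 0.07p at 16:14, 0.20p at 18:12 and 0.33p at 20:10. If the order is drawn by simple randomisation, the expected shift is 0 and its SD is p/√30 = 0.18p. On that assumption a split of 20:10 or worse has probability 2 × P(Bin(30, 0.5) ≤ 10) = 0.099.

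**Scale.** The 95% confidence half-width of each limit at n = 30 is about 2.045 × √(1/30 + 1.96²/(2 × 29)) = 0.65 s. At p/s = 0.5 the widening moves each limit by 0.23 s, roughly a third of that.

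**The case against.** Section 3.5 is a list of one-line method names, and an order term is the sort of detail that a statistical analysis plan may supply. A reader might infer that the protocol has decided to ignore order. The text does not support that: it is silent, and nothing in it contradicts anything else. This objection stands, and the point is therefore worded as a use of order that is not stated.

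A reader might also infer that the bias estimate is compromised. It is not. Randomising the order is the standard safeguard, and the expected shift is zero. Under simple randomisation the pooled SD contains p², so the pooled standard error, √(s² + p²)/√30, already reflects chance imbalance. Moreover, section 3.2.3 does not say that randomisation is simple; if it is blocked, imbalance hardly arises.

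Finally, a reader might carry the formula to p = s and report limits 41% too wide. That requires the mean differences in the two order groups to lie 2s apart, and no figure in the protocol suggests it. The fatigue sentence in section 8.3 is a general statement of participant risk, and section 8.4 provides rest as needed. Wider limits also err on the conservative side, since they make the new instrument look worse, and no stated decision depends on them.

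What survives is narrower. If the named analysis is run in its standard pooled form, any order effect that does exist goes into the SD of the differences, although it could be removed at negligible cost.

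**Conclusion.** The point holds as a minor, free improvement and not as an error in the protocol. The pooled Bland-Altman analysis is valid, and its bias is unbiased over the randomisation. Making no use of order would leave the limits about 0.5% to 12% wider than necessary for an assumed p/s of 0.1 to 0.5. It would also let the observed bias drift by chance with SD about 0.18p at n = 30 if randomisation is simple. Both results depend on p and s, which the protocol does not give; if there is no practice or fatigue effect, nothing is lost. Over that range the widening is smaller than the sampling uncertainty of each limit (about 0.65 s).

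**What to change.** Add to section 3.5, for the validation group:

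- Estimate the bias as the unweighted mean of the two order-specific mean differences (new minus conventional). The period effect then cancels whatever the split.
- Compute the limits of agreement around that bias from the within-order residual SD, on n − 2 degrees of freedom.
- Report the period effect with its 95% confidence interval. In the notation above, p is half the difference between the two order-specific means.

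Marking the order on the Bland-Altman plot would help the reader, as would a statement in section 3.2.3 of whether the order sequence is blocked.

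The cost is wording and one degree of freedom: at n = 30 the t multiplier goes from 2.045 to 2.048. With an uneven split the unweighted mean is slightly less precise than a pooled mean would be in the absence of any order effect. At 20:10 its standard error is ½ × √(1/20 + 1/10) = 0.194 s, against 1/√30 = 0.183 s. No extra patients or assessments are needed.

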### 3.2.2. Dosage and administration of the study drug, duration of administration

Not applicable in this study, as no drug therapy was used.

### 3.2.3. Case Registration and Allocation Methods

Participants who meet eligibility criteria will be randomly assigned to either the reliability or validity validation group using a random number table. Group assignment and randomization of assessment order will be performed using a computer-generated random number sequence by the study coordinator, who will not be involved in data collection.

## 3.3. Outcome

### 3.3.1. Main outcome

- ARAT

### 3.3.2. Secondary outcome

- Fugl-Meyer Assessment of the Upper Extremity (FMA-UE) 
- Box and Block Test (BBT) 
- Motor Activity Log (MAL) 
- Jikei Assessment Scale for Motor Impairment in Daily Living (JASMID) 

## 3.4. Clinical characteristics of the patient

Basic information: sex, age, height, weight, Body Mass Index, dominant hand side before stroke onset

Medical information: stroke type, stroke onset area, stroke onset date, paralytic side

## 3.5 Statistical analysis

Participant characteristics, clinical assessment data: descriptive statistics

Intra-rater reliability: ICC (2,1)

Inter-rater reliability: ICC (2,1)

Measurement error: standard error of measurement (SEM)

Minimum detectable change: MDC95

Item-level agreement: weighted kappa coefficient with quadratic weighting.

Criterion-related validity: Bland-Altman analysis, Bland-Altman plots.

Convergent validity: Correlation analysis

Analyses were performed using Jamovi version 2.6.44 (<https://www.jamovi.org>). The statistical significance level is 5%.

#### **4. Sample size and study period**

##### **4.1. Sample size**

Total of 60 participants.

##### **4.2. Basis for setting**

The sample size for reliability verification was calculated based on prior research, assuming ICC = 0.8, minimum acceptable ICC = 0.6,  $\alpha = 0.05$ , power  $(1 - \beta) = 0.8$ , two raters, and two measurements per participant . This calculation indicated a required sample size of 28–30 participants. For criterion-related validity, G\*Power 3.1 was used with an expected correlation coefficient  $r = 0.75$ ,  $\alpha = 0.05$ , and power = 0.95, yielding a minimum target sample size of 16 participants. Considering potential 10% data loss, 30 participants per group were planned.

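### The 28–30 participants for reliability correspond to four ratings in one ICC; each planned ICC uses two, so 30 participants give about 59–70% power, not 80%

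*Protocol*

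**What the plan says.** Protocol section 4.2 gives the planning values ("assuming ICC = 0.8, minimum acceptable ICC = 0.6"), alpha 0.05, power 0.8, and "two raters, and two measurements per participant". From these it states: "This calculation indicated a required sample size of 28–30 participants". It then allows for attrition: "Considering potential 10% data loss, 30 participants per group were planned".

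Section 3.2.1 describes what the reliability group provides. For intra-rater reliability, "a single examiner performs two new ARATs at 15-minute intervals". Video is taken at the initial assessment. For inter-rater reliability, "a second examiner scores the video recordings without knowing the results of the first examiner's scoring".

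Section 3.5 lists intra-rater and inter-rater reliability as two separate analyses, each an ICC(2,1). On the test level it says only "The statistical significance level is 5"%. Neither section says whether alpha is one- or two-sided, or how raters and measurements combine in the calculation.

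**The concern.** The number of ratings that enter an ICC largely determines the sample size needed to separate 0.8 from 0.6. Section 4.2 names two raters and two measurements without saying whether that means two ratings per ICC or four ratings in one ICC. Sections 3.2.1 and 3.5 settle what is analysed:

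- **Intra-rater ICC:** examiner 1, session 1 against session 2. Two scores.
- **Inter-rater ICC:** examiner 1 at session 1 against examiner 2 on the session 1 video. Two scores.

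If the calculation assumed more ratings than either ICC contains, the only power figure given for the two reliability objectives is too high.

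**Working it through.** **Inputs.** From section 4.2: ρ1 = 0.8, ρ0 = 0.6, alpha 0.05, power 0.80, 10% loss, 30 per group. From 3.2.1 and 3.5: k = 2 ratings per planned ICC. Sidedness is not stated, so both values are shown.

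**Formula** (hypothesis test for an ICC):

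n = 1 + 2k(zα + zβ)² / [(k − 1)(ln C0)²], with C0 = [1 + kρ0/(1 − ρ0)] / [1 + kρ1/(1 − ρ1)].

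(zα + zβ)² is (1.6449 + 0.8416)² = 6.183 one-sided and (1.9600 + 0.8416)² = 7.849 two-sided.

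**Reproducing the plan's figure (k = 4).** C0 = 7/17 = 0.4118 and (ln C0)² = 0.7873. Two-sided: n = 1 + 8 × 7.849 / (3 × 0.7873) = 27.6, so 28. This is the lower end of the stated range.

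**Two ratings per ICC (k = 2).** C0 = 4/9 = 0.4444 and (ln C0)² = 0.6576.

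- One-sided: n = 1 + 4 × 6.183 / 0.6576 = 38.6, so 39.
- Two-sided: n = 1 + 4 × 7.849 / 0.6576 = 48.7, so 49.

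| Ratings in one ICC (k) | One-sided n | Two-sided n |
|---|---|---|
| 2 | 39 | 49 |
| 3 | 27 | 33 |
| 4 | 22 | 28 |

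The k = 3 row is shown only because three scores exist per participant. Neither planned ICC combines all three.

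**Power with k = 2.** Power = Φ(√[(n − 1)(ln C0)²(k − 1)/(2k)] − zα).

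- n = 30: √(29 × 0.6576 / 4) = 2.183. One-sided Φ(2.183 − 1.645) = 0.705; two-sided Φ(2.183 − 1.960) = 0.588.
- n = 27 (30 × 0.9): √(26 × 0.6576 / 4) = 2.067. One-sided 0.664; two-sided 0.543.

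**Cross-checks.** Exact F-test power and a simulation of 40,000 runs agree with these power figures to within about 2 percentage points. The exact F-test sample sizes for k = 2 are 39 or 40 one-sided, depending on the error degrees of freedom, and 50 two-sided.

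**Loss allowance.** 28/0.9 = 31.1, so 32: a group of 30 does not cover the stated loss even from the plan's lower figure. With k = 2 the inflated numbers are 39/0.9 = 43.3, so 44, and 49/0.9 = 54.4, so 55.

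**What 30 can exclude with 80% power if the true ICC is 0.8.** For k = 2, 1 + 2ρ/(1 − ρ) = (1 + ρ)/(1 − ρ), which is 9 at ρ = 0.8. Write θ0 for its value at the minimum ICC.

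- One-sided: ln(9/θ0) = √(4 × 6.183 / 29) = 0.923, so θ0 = 3.574 and ρ0 = 2.574/4.574 = 0.56.
- Two-sided: ln(9/θ0) = √(4 × 7.849 / 29) = 1.040, so θ0 = 3.180 and ρ0 = 2.180/4.180 = 0.52.

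**The case against.** **The figure can be reproduced.** A reader might infer that 28–30 is an arithmetic slip that cannot follow from the stated inputs. The documents do not support that. Two raters and two measurements can be read as 2 × 2 = 4 ratings, and the formula then gives 28 two-sided. What fails is the match between that k and the design. Four ratings would require examiner 2 to score both sessions and all four scores to enter one ICC. Section 3.2.1 has the initial assessment filmed for examiner 2, and 3.5 keeps the two ICCs separate. That the authors used k = 4 remains an inference, because 4.2 does not show the calculation.

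**There is no success rule.** A reader might also infer a 30–41% chance that the study fails. The protocol sets no decision rule that the ICC must exceed 0.6. Section 3.5 mainly lists estimates: ICC, SEM, MDC95, kappa and Bland-Altman. This stands. The consequence is a wrong power statement and less precision than it implies, not a biased ICC or an invalid analysis. The stated power still has to be right, since 4.2 rests the sample size on it.

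**The gap depends on a guess.** With a true ICC of about 0.82 (one-sided) or 0.84 (two-sided), 30 participants reach 80% power against 0.6. That is so, and it limits the practical harm, but the plan assumes 0.8.

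**The 27 is conditional.** Section 5.2 lists loss of data as an exclusion, and the protocol does not say whether such participants are replaced. If they are, the figures for 30 apply.

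**Conclusion.** The concern holds as a mismatch between the calculation and the planned analyses. Each planned ICC uses two ratings, for which the stated inputs require 39 (one-sided) or 49 (two-sided) participants. Thirty give about 70% or 59% power, and 27 give about 66% or 54%. The 80% in section 4.2 is reached on neither sidedness.

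These figures assume a true ICC of 0.8, a minimum of 0.6 and the standard ICC test formula. The range reflects the unstated sidedness of alpha. An unseen statistical analysis plan would not remove the point, because the protocol itself states the inputs, the result and the power. The finding does not show that the study must enrol more participants.

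**What to change.** Correct section 4.2 only:

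1. State that each ICC is based on two ratings per participant, and whether alpha is one- or two-sided.
2. Replace the claim that 28–30 participants give 80% power with what the planned group delivers: about 70% (one-sided) or 59% (two-sided) with 30, and about 66% or 54% with 27. Alternatively, keep 80% power and restate the minimum ICC that 30 can exclude if the true ICC is 0.8: about 0.56 one-sided or 0.52 two-sided.
3. Correct the attrition sentence so that it no longer implies that 30 covers a 10% loss from 28; that would take 32.

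The cost is a rewording and a less favourable stated power. No additional participants, video recording or scoring are needed.

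### Criterion validity is sized by a correlation calculation but analysed by Bland-Altman, so the stated 0.95 power and minimum of 16 do not describe the planned analysis

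*Protocol*

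**What the plan says.** Section 4.2 treats the two groups separately. For criterion-related validity, G\*Power 3.1 "was used with an expected correlation coefficient" of 0.75, with alpha 0.05 and power 0.95, "yielding a minimum target sample size of 16 participants". The section names neither the null hypothesis nor the sidedness. It ends: "Considering potential 10% data loss, 30 participants per group were planned". Section 4.1 gives the total of 60.

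Section 3.5 assigns one analysis to each aim. For the comparison of the two instruments it says "Criterion-related validity: Bland-Altman analysis, Bland-Altman plots". The only correlation it lists is on another line: "Convergent validity: Correlation analysis". Section 2.1 keeps these aims apart: criterion-related validity is against the conventional ARAT, and convergent validity is with established clinical measures.

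**The concern.** A power figure belongs to a particular test. The one in section 4.2 belongs to a test on a correlation coefficient, and section 3.5 plans no such test for the new against the conventional ARAT. What it plans is an estimate of the mean difference and the limits of agreement, and the protocol gives no expected precision, SD of the differences or acceptable limit for these.

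The two methods also answer different questions. A correlation above zero shows that the two versions rank patients in a broadly similar way. It does not show that a score from one can stand in for a score from the other, which is what the transition described in section 2.1 needs. At stake is the justification: a reader would take criterion validity to be covered at 95% power, with 16 participants as enough, when neither figure applies to the result that will be reported.

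**Working it through.** **Inputs.** Section 4.2: r = 0.75, alpha 0.05, power 0.95, minimum 16, 10% loss, 30 per group. Section 3.5: Bland-Altman for criterion validity. The SD of the differences, the expected bias and the acceptable limit are not given.

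**1. Reproducing the 16.** Power of the test of rho = 0 when the true correlation is 0.75, under a bivariate normal model:

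| Calculation | Result |
|---|---|
| Exact, two-sided 5% | power 0.937 at n = 15, 0.952 at n = 16; minimum 16 |
| Fisher z, two-sided | ((1.960 + 1.645) / atanh(0.75))² + 3 = (3.605 / 0.973)² + 3 = 16.7; minimum 17 |
| Exact, one-sided | minimum 14 |
| Fisher z, one-sided | minimum 15 |
| Fixed-predictor t test, two-sided | minimum 13 |

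Of these, only the exact two-sided test of zero correlation gives 16. The arithmetic in section 4.2 is right for its own inputs, and the match identifies the test.

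**2. How little that test asks.** With 30 pairs, the two-sided 5% critical value is r = t / √(t² + 28), with t = 2.048 on 28 degrees of freedom, so r = 0.36. Any larger correlation between the two versions would count as significant.

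**3. What sets the group size.** Allowing for 10% loss, 16 / 0.9 = 17.8, so 18. The plan is 30, which is in line with the 28–30 that section 4.2 gives for reliability. The 16 does not drive the number recruited.

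**4. Precision of the analysis that is planned.** In units of the SD of the paired differences, assuming roughly normal differences, the 95% confidence interval half-widths are:

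- mean bias: t / √n
- each limit of agreement: t × √(1/n + 1.96² / (2(n − 1)))

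where t is the 97.5% point on n − 1 degrees of freedom.

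| Pairs | t | Mean bias | Each limit of agreement |
|---|---|---|---|
| 30 (planned) | 2.045 | 2.045/√30 = 0.37 | 2.045 × √(0.0333 + 0.0662) = 0.65 |
| 27 (30 × 0.9) | 2.056 | 2.056/√27 = 0.40 | 2.056 × √(0.0370 + 0.0739) = 0.68 |
| 16 (stated minimum) | 2.131 | 2.131/√16 = 0.53 | 2.131 × √(0.0625 + 0.1281) = 0.93 |

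**5. Whether 30 is enough.** This depends on an acceptable limit that the protocol does not state. Assuming zero bias, the simulated probability that both limits, with their 95% confidence intervals, lie within ±delta is:

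| Assumed delta (SD of differences) | n = 27 | n = 30 |
|---|---|---|
| 2.5 | 0.24 | 0.26 |
| 3.0 | 0.73 | 0.78 |
| 3.5 | 0.97 | 0.98 |

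These limits are illustrations, not values from the protocol. The range shows that a power of 0.95 cannot be carried over from the correlation test, and that adequacy cannot be settled either way without a stated limit.

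**The case against.** The best defence is that nothing in the conduct of the study depends on the 16. Thirty per group are planned, Bland-Altman is a suitable method for comparing two instruments, and recruitment and data collection would be the same without the sentence. This stands, and it limits the point to the sample-size rationale. It does not remove the point, because the protocol itself fixes both the calculation and the analysis, and they do not match. A separate analysis plan could add detail but would not make the power statement in section 4.2 apply to section 3.5.

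It is also fair to say that the null of zero correlation is not written down. It is an inference, though a firm one. The mismatch does not rest on it: whichever correlation test was meant, none is listed for criterion validity.

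Three stronger readings are tempting and are not supported:

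- **The validation group is too small.** The ±0.93 SD at 16 pairs describes no planned group. At 30 or 27 pairs the half-widths are ±0.65 or ±0.68 SD, and nothing in the protocol shows these to be inadequate. Section 8.4.2 allows early termination if the objectives are met, but does not tie this to 16.
- **The power claim fails for the study's central question.** Section 2.1 lists intra-rater reliability, inter-rater reliability, criterion-related validity and convergent validity without ranking them. Section 3.3.1 names only the ARAT as main outcome.
- **The plan would accept limits of agreement of ±1.39 SD of the score.** That figure, 1.96 × √(2 × (1 − 0.75)), follows from r = 0.75 only with equal SDs and zero bias. It turns a sizing input into a forecast, and the protocol sets no acceptance rule of that kind.

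**Conclusion.** The point holds as an internal mismatch, and it should be fixed. The 0.95 power and the minimum of 16 belong to a correlation test, most plausibly the two-sided test of rho = 0, while the planned criterion-validity analysis is Bland-Altman alone. The stated power therefore says nothing about how well the bias and the limits of agreement will be estimated.

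The consequence is limited. The planned 30 is well above 16 and need not change. The precision figures assume roughly normal differences and are in units of an SD that the protocol does not give, so they cannot be turned into ARAT points from this document and do not alone show that 30 is adequate.

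**What to change.** In section 4.2, withdraw the claim of 0.95 power and a minimum of 16 for criterion validity. State instead the precision that the planned group gives: with 30 pairs (27 after 10% loss), 95% confidence interval half-widths of about ±0.37 (±0.40) SD of the differences for the mean bias and ±0.65 (±0.68) SD for each limit of agreement.

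In section 3.5, say that these confidence intervals will be reported with the Bland-Altman plot and read against an acceptable difference in ARAT points, fixed and justified before the data are examined. Without that difference, the widths alone cannot support a conclusion about agreement.

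If a correlation between the new and the conventional ARAT was intended, list it in section 3.5 as a supplementary criterion-validity analysis and say in section 4.2 that the 0.95 power refers only to that test. The agreement precision should still be stated.

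The cost is a few sentences of protocol text, a few extra confidence intervals and a decision on the acceptable difference. No further participants or measurements are needed.
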